### Endpoints and sample size calculation

The scales and questionnaires in this study have been used in several international studies investigating palliative care in dementia, including the Netherland’s Dutch End of Life (DEOLD) study. A recent review has indicated good psychometric properties in tests of palliative care such as the *Discomfort Scale for Dementia of the Alzheimer Type (DS-DAT),* which offers high internal consistency [17]*.*

Primary outcomes of EPYLOGE include patients’ quality of life, as measured by the *Quality of Life in Late Stage Dementia-Scale (QUALID)* [18], and quality of death, as measured by the *Comfort Assessment of Dying with Dementia-Scale (CAD-EOLD)* [8]). These assessments of quality of life and death will be compared between YOD and LOD patients. Secondary outcomes include symptom burden and symptom management, comfort measures, caregivers’ burden, satisfaction with care and shared-decision making as well as health care utilization. These secondary outcomes will be measured by a variety of scales and questionnaires. The impact of living situation (home/nursing home), gender, social status and residence (rural vs. metropolitan area) on the primary endpoints will be assessed.

Sample size calculation for the comparison of persons with YOD and LOD was performed using the primary endpoints. Bonferroni adjustment for multiple comparisons was utilized. The global significance level was set to 5%. For part A, the comparison of persons with YOD and LOD in advanced stages of dementia, the quality of life, as measured by the *Quality of Life in Late Stage Dementia-Scale (QUALID)* [18]), was chosen as the primary endpoint. Scale characteristics include: a near-normal distribution, a range of 11 to 55 in which lower scores reflect higher quality of life during the last seven days of life, a mean of 22.76, a standard deviation of 7.40, and a hypothesized clinically meaningful difference of 5 points. A sample size of 86 persons with dementia within each group will have 89% power in detecting a difference in mean QUALID scores of 4, assuming that the common standard deviation is 7.4 and that the two-sided independent samples t-test used will have 2.5% local significance. Assuming a drop-out rate of 14%, at least 100 persons per group will be required, comprising a total of 200 persons.

For part B, the comparison of persons with YOD and LOD at end of life, the quality of death, as measured by the *Comfort Assessment of Dying with Dementia-Scale (CAD-EOLD)* [8]), was chosen as the primary endpoint. Scale characteristics include: a near-normal distribution, a range of 14 to 42 in which higher scores reflect better comfort level, a mean of 31.4, a standard deviation of 5.9, and a hypothesized clinically meaningful difference of 3 points. A sample size of 43 persons with dementia in each group will have 80% power in detecting a difference in mean CAD-EOLD scores of 4, assuming that the common standard deviation is 5.9 and that the two-sided independent samples t-test used will include 2.5% local significance. Assuming a drop-out rate of 14%, at least 50 recent cases of deceased persons per group will be required for part B.

### Statistical analysis

Primary endpoint analysis: The two groups (YOD and LOD) will be compared with respect to both primary endpoints. The two-sided independent samples t-test will be used to test for differences in both primary endpoints. The global significance level will be set to 5%. The local significance level of each test (Bonferroni adjustment) will therefore be 2.5%.

Secondary endpoint analysis: Analyses of baseline data and secondary endpoints will be performed using appropriate descriptive statistics and independent samples tests for differences between the two study groups. All tests will be two-sided with an exploratory significance level of 5%.

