### Subjects

Dyads of persons with advanced dementia, who live at home or in LTC, and their family caregivers are identified in multiple ways: 1) Through the Center of Cognitive Disorders at the University Hospital of the Technical University of Munich: The family caregivers of persons with a diagnosis of a neurodegenerative dementia, who have been seen in the outpatient clinic since 2005, are contacted. If the person with dementia fulfills the inclusion criteria, he or she, and the corresponding family caregiver will be invited to participate in the study; 2) Through a collaborative network specialized in YOD in order to include a sufficiently high number of persons with YOD (in spite of its relatively low prevalence), institutions specialized in YOD (i.e. nursing homes, support centers, research centers, etc.) are asked to establish contact with families of persons with advanced YOD; 3) through LTC units in urban and rural areas of Germany. Lack of informed consent either from the person with dementia (or their legal surrogate) or from their family caregiver is an exclusion criterion.

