**Fig. 1 Fig1:**
[figure not shown]
EPYLOGE: Flow chart of study design and procedures

In **part A** (baseline-visit), palliative care issues in advanced dementia are analyzed and compared between 100 persons with YOD and 100 persons with LOD. Studies have shown that in Germany about 50% of persons with advanced dementia are cared for at home [2]. Thus, the objective is to include approximately 50 persons living at home and 50 persons living in LTC in each group.

After the baseline visit, family caregivers are contacted by phone every three months in order to briefly assess changes of the living and care situation. The phone calls are continued until the death of the person with dementia or until the end of study. After the patient’s death assessment B will be performed within 3 months at the latest.

In **part B** (follow-up visit) palliative care issues at the end of life are analyzed and compared between 50 deceased persons with YOD and 50 deceased persons with LOD identified by the phone calls described above. It is anticipated that about 50% of the participants in part A will die during the study period. In case this assumption is not true and fewer participants die, or if deaths are more common in specific subgroups (age, living situation), the groups in part B are completed with additional bereaved families.

In **part C**, the results of part A and B will be discussed in an expert round table that is scheduled for early 2020. Expert consensus recommendations will concern strategies and interventions in order to improve palliative care in YOD and LOD.

In **part D** the expert consensus recommendations will be disseminated.

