If the person with dementia lives in an LTC facility, the administrator is asked to provide a detailed and standardized description of the facility, infrastructure, organization, service provision, and palliative care provision.	

After part A, the respective family caregiver is perdiocially phoned every three months and changes regarding living situation, care provision and comorbidities are assessed. The post-mortem visit (part B) is arranged if the person with dementia has died.

In **part B** - end-of life issues in advanced dementia: standardized post mortem assessments are performed with the family caregivers of 50 persons with YOD and 50 persons with LOD at a follow-up visit.

In part B, a standardized interview with the bereaved family caregiver is performed less than three months after the person with dementia has died. Instruments and measures are described in Table 2.

**Table 2 Tab2:** Part B, follow-up visit with family caregiver post-mortem: instruments and measures

Interviews of the family caregiver	
Symptoms, treatment and care before death and circumstances of death as reported by the caregiver and identified by retrospective evaluation of medical and care files; evaluation if advance directives have been applied.	
Caregiver satisfaction with care: End of Life in Dementia-Satisfaction with Care (EOLD-SWC) (Volicer L et al., [8])	
Burden: Modified version of Burden Scale for Family Caregivers (BSFC)	
Patient suffering: Mini Suffering State Examination (MSSE)	
Quality of life: Modified version of Quality of Life in Late Stage Dementia (QUALID)	
Symptom management: End of Life in Dementia-Symptom Management (EOLD-SM) (Volicer L et al., [8])	
Persons with dementias comfort in dying: Comfort Assessment of Dying with Dementia (CAD-EOLD) (Volicer L et al., [8])	
Caregiver wellbeing: WHO five (WHO-5)	
Caregiver depression: Beck Depression Inventory II (BDI II)	
Open questions: Caregivers’ problems, challenges, barriers, needs, preferences regarding end-of-life care.	
Description - LTC	
If the person with dementia lives in an LTC facility, the administrator is asked to provide a detailed and standardized description of the facility, infrastructure, organization, service provision, and palliative care provision.	

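### The primary t-tests ignore possible correlation among residents of the same LTC facility; if homes contribute several participants from mainly one group, the 2.5% level can be exceeded

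*Protocol article*

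**What the plan says.** - **Test (Statistical analysis).** "The two-sided independent samples t-test will be used to test for differences in both primary endpoints". The global level is 5% and Bonferroni gives 2.5% per endpoint. No facility term or variance adjustment is mentioned.
- **Sample size (Endpoints and sample size calculation).** For part A: "A sample size of 86 persons with dementia within each group will have 89% power in detecting a difference in mean QUALID scores of 4". The SD is taken as 7.4 in both groups. Part B has 43 per group and 80% power for a CAD-EOLD difference of 4 with SD 5.9. Both use the independent-samples t-test at 2.5%. The same section will assess how home versus nursing home affects the primary endpoints.
- **Where participants live (Study design, part A).** The target is "approximately 50 persons living at home and 50 persons living in LTC in each group".
- **Recruitment (Subjects).** There are three routes: the university memory clinic, a network of YOD-specialised institutions that includes nursing homes, and "through LTC units in urban and rural areas of Germany".
- **Facility data (Instruments and measures, Tables 1 and 2).** For participants in LTC, "the administrator is asked to provide a detailed and standardized description of the facility".
- **Main source (Discussion).** Most patients are expected to come through the memory clinic.

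**The concern.** Two of the three recruitment routes can supply several residents from one home. Those residents share staff, routines and palliative care provision. The article itself treats facilities as differing in care: it collects a description of each one, and its Discussion presumes that homes weak in palliative care may decline to take part. QUALID and CAD-EOLD scores may therefore be correlated within a home.

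The effect on the YOD versus late-onset dementia (LOD) comparison depends on how homes divide between the groups. If a home contributes mainly to one group, as a YOD-specialised home would, its shared effect does not cancel in the group difference. The t-test standard error is then too small. At stake are the level of both confirmatory tests, the width of their confidence intervals and the stated power. Adding home versus nursing home as a factor would not help, because it does not separate one nursing home from another.

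**Working it through.** **Inputs from the article.** n = 86 per group, difference 4, SD 7.4 (part A); n = 43 per group, difference 4, SD 5.9 (part B); two-sided local level 2.5%; about half of each group in LTC.

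**Assumed inputs (not in the article).** s is the share of each group living in homes that contribute more than one participant, m is participants per such home, and ICC is the intra-facility correlation. I take s = 0.25 or 0.5, m = 1 to 10, and ICC = 0.05 to 0.10. The value s = 0.5 places every LTC resident in a cluster, so it is the upper bound on the share.

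**Step 1: reproduce the stated figures under independence.** Noncentrality = difference / [SD × √(2/n)].
- Part A: 4 / [7.4 × √(2/86)] = 3.54. Exact noncentral t power is 89.9% (stated 89%).
- Part B: 4 / [5.9 × √(2/43)] = 3.14. Power is 80.4% (stated 80%).
- Dropout: 86/0.86 = 100 and 43/0.86 = 50, as stated.

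The stated figures are sound if observations are independent.

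**Step 2: variance with group-specific homes.** Among n persons, the n·s who are clustered each have m − 1 housemates with correlation ICC, so

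Var(mean) = (SD²/n) × DE, with DE = 1 + s(m − 1)ICC.

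The unadjusted t-test then has true level 2 × [1 − Φ(2.2414/√DE)]. Power of a test with the correct standard error is taken from the noncentral t with n/DE per group.

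**Step 3: part A.**

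| s | m | ICC | DE | True local level | Power with correct SE |
|---|---|---|---|---|---|
| any | 1 | any | 1.00 | 2.5% | 89.9% |
| 0.25 | 5 | 0.05 | 1.05 | 2.9% | 88.3% |
| 0.25 | 5 | 0.10 | 1.10 | 3.3% | 86.7% |
| 0.5 | 5 | 0.05 | 1.10 | 3.3% | 86.7% |
| 0.5 | 5 | 0.10 | 1.20 | 4.1% | 83.3% |
| 0.5 | 10 | 0.10 | 1.45 | 6.3% | 74.9% |

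Worked row: s = 0.5, m = 5, ICC = 0.10 gives DE = 1 + 0.5 × 4 × 0.10 = 1.20. Then 2.2414/√1.20 = 2.046, a two-sided tail of 4.1%. At m = 2 and s = 0.5 the level is only 2.7% to 2.9%.

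Simulated null t-tests (40,000 runs, n = 86, s = 0.5, ICC 0.10) gave 4.0% at m = 5 and 6.3% at m = 10, in line with the formula.

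**Step 4: part B.** The article expects about half of part A participants to die, so clusters should be roughly halved.
- m = 5 becomes 2.5. With s = 0.5 and ICC 0.10, DE = 1 + 0.5 × 1.5 × 0.10 = 1.075, level 3.1%, power 77%.
- m = 10 becomes 5. With the same s and ICC, DE = 1.20, level 4.1%, power 72%.

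**Step 5: other arrangements of homes.**
- Only YOD residents cluster (s = 0.5, m = 5, ICC 0.10): DE = (1.20 + 1)/2 = 1.10, level 3.3%.
- Homes shared equally by both groups: simulated level 1.8% to 2.5% (s = 0.5, m = 2 to 10, ICC 0.05 to 0.20). The shared effect cancels and the t-test is, if anything, conservative.

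**The case against.** A reader might infer that homes are largely specific to YOD or to LOD, and hence that the 2.5% level is in fact exceeded. The article does not support either step. Under Subjects, only the YOD network is called specialised, and it also includes support and research centres. The other LTC units are not restricted to LOD. If homes hold both groups, the direction of the error reverses (step 5).

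Three further points stand:

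- **Main source.** If most patients come through the memory clinic, those now in LTC may be spread over many homes, often one per home. This argues for s below 0.5 and a small m.
- **Shared informant.** It is tempting to add that one nurse may rate several residents. Table 2 places CAD-EOLD in the family caregiver interview, so this does not apply there. For QUALID in part A, nursing staff are used only where necessary. This favours the lower end of the ICC range.
- **Part B.** Part A cluster sizes cannot be carried over unchanged. If deaths are too few or unevenly spread, part B is filled with further bereaved families, whose facilities are unknown.

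It can also be said that a condensed article leaves variance adjustments to a full analysis plan. That has limited force here, because the article states the primary test and sizes the study on it.

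These points limit the size of the problem. They do not show that the independence assumption is safe, because the plan does not control how participants fall into homes.

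**Conclusion.** The point holds in conditional form. The stated test and power ignore possible correlation within LTC facilities, in a design that places about half of each group in LTC and recruits partly through facilities. Exceeding 2.5% requires three things together: several participants per home, a positive ICC, and homes that mostly hold one group.

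Where all three apply, the likely excess is modest: a local level of about 2.9% to 4.1% at five participants per home, with part A power some 2 to 7 points below the 89.9% obtained under independence. The 6.3% figure needs every LTC resident clustered ten to a home with ICC 0.10, and should be read as an upper-bound case. In part B, halved clusters give about 3.1% and 77% power at s = 0.5 and ICC 0.10. All of this rests on assumed s, m and ICC. The change is still worth making, because it costs little and protects the level however the homes turn out to be distributed.

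**What to change.** Replace the t-test for both primary endpoints with a linear model of group that accounts for facility. Either a random facility intercept or cluster-robust standard errors with a small-sample correction will do. Treat each home-living person as their own cluster, and keep the 2.5% local level. Report the number of facilities and the residents per facility by group, so that a reader can see whether clustering matters.

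The cost is a change of analysis wording. Facility should be identifiable from the description already requested from each administrator, so no new data are needed. Confidence intervals will be slightly wider if clustering within group-specific homes is present. If it is not, the result will be close to the t-test.

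### Fixed Bonferroni at 2.5% per primary test is valid, but Holm's step-down gives more power at the same 5% familywise level, mainly for Part B

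*Protocol article*

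**What the plan says.** The protocol article, section Statistical analysis, compares YOD and LOD on both primary endpoints: "The two-sided independent samples t-test will be used to test for differences in both primary endpoints". It adds "The global significance level will be set to 5" percent, and then "The local significance level of each test (Bonferroni adjustment) will therefore be 2.5" percent. The level for one endpoint does not depend on the result for the other.

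The section Endpoints and sample size calculation uses the same rule: "Bonferroni adjustment for multiple comparisons was utilized. The global significance level was set to 5" percent. For Part A, "A sample size of 86 persons with dementia within each group will have 89% power in detecting a difference in mean QUALID scores of 4". The SD used there is 7.4. For Part B, "A sample size of 43 persons with dementia in each group will have 80% power in detecting a difference in mean CAD-EOLD scores of 4". The SD used there is 5.9. Both calculations use a local two-sided 2.5%. The differences named as clinically meaningful are not the ones used for power. For QUALID the text gives "a hypothesized clinically meaningful difference of 5 points", and for CAD-EOLD it gives 3 points.

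**The concern.** With two primary hypotheses and a global 5%, fixed Bonferroni holds each test at 2.5% even after the other has been rejected. Once one hypothesis is rejected at 2.5%, the other can be tested at the full 5% without raising the familywise error rate. That is Holm's procedure, and it needs no assumption about how the two tests are correlated.

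The point matters here because the two parts differ in strength. Part A is planned with 86 evaluable persons per group and Part B with 43. If the assumed QUALID difference exists, Part A will usually reject, and its 2.5% could then be passed to the quality-of-death comparison. The fixed rule leaves it unused. Part B depends on deceased cases, and the plan already allows for adding bereaved families if too few participants die, so power gained without extra cases is worth having.

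**Working it through.** **Inputs** (Endpoints and sample size calculation; Statistical analysis). Part A: n = 86 per group, SD 7.4, planned difference 4, clinically meaningful difference 5. Part B: n = 43 per group, SD 5.9, planned difference 4, clinically meaningful difference 3. Two-sided t-tests, local level 2.5%, global level 5%.

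**Power formula.** For true difference Δ, the noncentrality is δ = Δ / (SD × √(2/n)) with 2n − 2 degrees of freedom. Power is P(|T| > c), where T is noncentral t and c is the two-sided critical value.

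**The plan's own figures reproduce.**
- Part A, Δ = 4: δ = 4 / (7.4 × √(2/86)) = 3.545 and c = 2.261 at 2.5%, so power is 89.9% (stated 89%).
- Part B, Δ = 4: δ = 4 / (5.9 × √(2/43)) = 3.144 and c = 2.282 at 2.5%, so power is 80.4% (stated 80%).

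**Powers needed for the comparison.**

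| Test | True difference | Power at 2.5% | Power at 5% | Gap |
|---|---|---|---|---|
| B (CAD-EOLD) | 3 | 53.2% | 64.5% | 11.2 points |
| B (CAD-EOLD) | 4 | 80.4% | 87.4% | 7.1 points |
| A (QUALID) | 2 | 31.5% | | |
| A (QUALID) | 3 | 65.4% | | |
| A (QUALID) | 4 | 89.9% | 94.1% | 4.2 points |
| A (QUALID) | 5 | 98.4% | 99.3% | 0.8 points |

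**Holm.** Part B is rejected if its p-value is at most 2.5%, or if it is at most 5% and Part A's is at most 2.5%. With independent tests:

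Holm power for B = (B at 2.5%) + (A at 2.5%) × [(B at 5%) − (B at 2.5%)].

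Example with QUALID difference 4 and CAD-EOLD difference 4: 0.8037 + 0.8992 × 0.0707 = 0.8673.

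| True QUALID difference | Part B at 3 points (now 53.2%) | Part B at 4 points (now 80.4%) |
|---|---|---|
| 5 | 64.3% (+11.1) | 87.3% (+7.0) |
| 4 | 63.3% (+10.1) | 86.7% (+6.4) |
| 3 | 60.6% (+7.3) | 85.0% (+4.6) |
| 2 | 56.8% (+3.5) | 82.6% (+2.2) |
| 0 | 53.5% (+0.3) | 80.5% (+0.2) |

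**Other quantities.**
- Part A at a QUALID difference of 4 rises from 89.9% to 92.2% (CAD-EOLD difference 3) or 93.3% (difference 4).
- Power to reject both hypotheses at 4 and 4 points rises from 72.3% to 82.0%.
- The chance of rejecting at least one hypothesis does not change, because both rules start from the smaller p-value against 2.5%.
- Reaching 86.7% in Part B under fixed Bonferroni at 4 points would take 51 evaluable persons per group instead of 43. With 14% drop-out that is 51 / 0.86 = 59.3, so 60 instead of 50.

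**Dependence.** Part B draws largely on Part A participants, so independence is a simplification. Simulation with assumed correlations of 0.3 and 0.5 between the test statistics, for QUALID differences of 4 and 5, changed the Part B gain by less than 1 point.

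**The case against.** The strongest reply is that nothing is wrong. Fixed Bonferroni is valid and prespecified, it is applied in the same way in both sample size calculations and in the analysis, and the stated powers reproduce at that level. All of this stands, so the point is one of efficiency.

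A reader might infer that Part B loses about 11 points of power in general. The documents do not support this. That figure needs a true CAD-EOLD difference of 3 and a QUALID difference near 5. It is also close to the ceiling: the gap between testing Part B at 5% and at 2.5% peaks at 11.5 points, at a difference of about 2.7. At the planned 4 points the gain is 6 to 7.

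A reader might also infer that Part A will reject in most situations where YOD and LOD differ. That holds only for QUALID differences of about 4 to 5 points. The Background section says the expected YOD/LOD differences are still unconfirmed. At a QUALID difference of 2, Part A rejects 31.5% of the time and there is little to pass on.

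The last objection concerns reporting, and it stands. Every additional rejection under Holm has a p-value between 2.5% and 5%. In exactly those cases a 97.5% confidence interval includes zero while the test is declared significant, so the mismatch covers the whole of the gain. Recruitment began in October 2017, so the change would also be an amendment to a running study.

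**Conclusion.** The point holds as a cheap improvement. Fixed Bonferroni is uniformly less powerful than Holm at the same global two-sided 5%. If the true QUALID difference is 4 to 5 points, Holm lifts Part B from 80% to about 87% at the planned 4 points, and from 53% to about 63-64% at the clinically meaningful 3 points. The gain shrinks with the QUALID difference and is close to zero if there is none, but power never falls below its present value. Familywise control under Holm does not depend on independence. The power figures take the tests as independent and use the plan's standard deviations and evaluable numbers.

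It would be too strong to read this as a repair of Part B. Part B was powered for 4 points while 3 is named as clinically meaningful, and Holm leaves it at about 64% at best for 3 points. That mismatch is a separate matter and needs its own answer.

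**What to change.** Before the primary data are examined, amend the primary endpoint paragraph in the section Statistical analysis. Replace the fixed local level with wording such as: the two primary hypotheses are tested by Holm's step-down procedure at a global two-sided level of 5%; the smaller p-value is compared with 2.5% and, if that hypothesis is rejected, the other is compared with 5%.

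Add two clarifications:
- The Holm decision governs the claim of significance. 97.5% confidence intervals are still reported, with a note that an interval may include zero when the p-value lies between 2.5% and 5%.
- A primary p-value at or below 2.5% can be declared significant at once. One between 2.5% and 5% waits for the other endpoint. Any delay is small in practice, since the expert round table in Part C already waits for both parts.

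Keep the sample size as planned: power under Holm is at least what the plan's calculation gives at 2.5%. The cost is a few sentences, a dated amendment, and the looser match between intervals and test decisions.
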